#### Control group

2.3.3

The control group receives the usual academic lessons during the 16-weeks of intervention, without methodological modification or inclusion of breaks that could alter the usual levels of PA during school hours.

### Measures

2.4

Participants are assessed at baseline (January 2023), post-intervention (May 2023), and 1 month after the intervention (June 2023) to test the stability over time of the strategies offered to teachers. Post-intervention measure of accelerometers-based variables and time-on-task are assessed during the last weeks of intervention, due to the characteristics of the indicators. To minimize variability in assessments, all measurements are conducted in schools by trained researchers who have received prior training.

#### Primary outcome measures

2.4.1

##### Physical activity and sedentary time

2.4.1.1

Actigraph (Actigraph GT3X+, Inc., Pensacola, FL, USA) is used to measure PA and sedentary time. Participants wear the monitor for eight consecutive days. To ensure a higher compliance rate when wearing the device, it was decided that participants would wear it on the non-dominant wrist, as this is an area that has been shown to be just as valid as on the waist (34). Participants are instructed to wear the accelerometer throughout the day (including sleeping hours), except for aquatic or situations where the device may come into contact with water. Sleep duration is captured through self-reported data, wherein each participant is provided with an accelerometer diary. Participants are required to diligently record the times at which they initiate sleep and awaken each day while wearing the accelerometer.

The screening and data collection procedures are conducted following the established protocols used in previous studies involving adolescents (34). Data will be downloaded and analyzed by using the ACTILIFE software (v.6.11.7 Actigraph TM). Inclusion criteria for the analyses are: (i) at least 3 days of valid weekday data and at least 1 day of valid weekend data; (ii) a minimum of 10 h of recording per day (34, 35).

#### Secondary outcome measures

2.4.2

##### Health-related physical fitness

2.4.2.1

Those tests comprising the High Priority ALPHA Health-Related Fitness Test Battery (36) are used to assess HRPF:

*20-m shuttle run test* is used to assess cardiorespiratory fitness. Two lines are marked on the track 20-m apart. Participants run back and forth between the lines, following a straight trajectory, and matching the rhythm of an audio recording. The initial speed is 8.5 km/h and is increased by 0.5 km/h per leg (each leg corresponds to 1 min). The test ends when the participant stops due to fatigue or when he does not cross the lines marked to the pace of the acoustic signals on two consecutive occasions. The test is performed once, and the last stage or half stage completed by the participant is scored.

*Hand grip test* is used to assess upper body maximal isometric muscular fitness. A validated hand-held dynamometer with an adjustable grip (TKK 5101 Grip D; Takey, Tokyo, Japan) is used. Prior to the test, the dynamometer’s grip is adjusted to the size of the participant’s hand (37). During the test, the participants stand upright and hold the dynamometer in one hand. They progressively squeeze the dynamometer until maximum force is developed, maintaining the pressure for at least 2 s, while ensuring that the elbow, arm, and trunk remain stable and unmoving. The test is performed twice, alternating between each hand. The maximum score achieved with each hand is recorded in kilograms, and the mean value between the two scores is calculated and saved for further analysis.

*Standing broad jump test* is used to lower body explosive muscular fitness. The participants stand behind a line with feet shoulder width apart. Then, with a slight swing, the participant is asked to jump forward as far as possible with both feet. If the participants rest his hands or lifts his feet off the ground on landing, the test is invalid. The test is performed twice, and the best score attained is recorded in centimeters for analyses.

*Body mass index and waist circumference* is used to assess body composition. For body mass measurement, participants stand barefoot on an electronic scale (type SECA 861; range, 0.05–130 kg; accuracy, 0.05 kg). Height measurement is taken in the Frankfort plane using a telescopic height measuring instrument (type SECA 225; range, 60–200 cm; accuracy, 1 mm). Each measurement is taken twice, and the mean of the two measurements is recorded. Body mass index is calculated as weight/height squared (kg/m2). On the other hand, waist circumference is measured using a non-elastic tape (SECA 200; range, 0–150 cm; accuracy, 1 mm). The tape is placed in the frontal plane at the midpoint between the superior iliac spine and the costal border at the mid-axillary line. The measurement is taken twice, and the mean of the two measurements is recorded.

Additionally, self-reported physical fitness level is measured through the International Fitness Scale (IFIS) (38). This scale has proven to be a valid instrument to correctly classify a sample of adolescents from different European countries according to their physical fitness levels (38). The scale is based on responses to five physical fitness questions: overall FP, cardiorespiratory fitness, muscle fitness, speed-agility, and flexibility. Participants are asked to rate each of the FP components on a 5-point Likert-type scale ranging from: “very poor” (1); “poor” (2); “acceptable” (3); “good” (4) and “very good.”

##### Academic indicators

2.4.2.2

###### School engagement

2.4.2.2.1

The engagement scale validated in adolescents and university students (UWES-S-9) (39, 40) is used to evaluate school engagement. The UWES-S-9 is composed of nine items that reflect the three dimensions of engagement: (i) vigor; (ii) absorption; and (iii) dedication, each dimension is represented by three items that are evaluated through a Likert-type scale, ranging from “never” (0 points) to “always” (6 points).

###### Learning perception

2.4.2.2.2

Learning perception in mathematics is assessed by the questionnaire developed by Abella et al. (41). The questionnaire consists of eight items that measure two dimensions: “perceived learning” (items 1–4) and “satisfaction with learning” (items 5–8). Participants rate their agreement with each item on a five-point Likert scale, with “1” indicating “strongly disagree” and “5” indicating “strongly agree.”

###### Academic performance

2.4.2.2.3

It is evaluated through the marks reported by the schools in the three official evaluations of the academic year, specifically in January, April, and June.

###### Mathematical fluency test

2.4.2.2.4

Mathematical fluency test is assessed by means of test number 6 of the *Batería* III Woodcock-Muñoz™ (42) (age range 2–90 years old). This battery has been validated to specifically measure academic achievement in math. In this test, participants are given a three-minute period to perform as many simple mathematical calculations as possible.

###### Time-on task

2.4.2.2.5

Time-on task is evaluated in mathematics classes or the time at which the AB are to be held and in the consecutive class 1 h later. Students’ on-task behavior was graded attending to the guidelines used Mahar et al. (43) in on-task and off-task. On one hand, on-task behavior is characterized by students making eye contact with the teacher and actively following the teacher’s instructions or class rules. On the other hand, off-task behavior is identified when students fail to pay attention or break class rules. In turn, off-task behavior is further categorized into three subtypes: (i) off-task-motor (any motor response that breaks the rules and/or disrupts the learning situation); (ii) off-task-noise (any oral response that breaks the classroom rules and/or disrupts the learning situation) and (iii) off-task-passive (moments when the student does not participate in any interaction or do anything when expected to participate).

During each assessment, a researcher observes six students. Each investigator has 15 s to observe and identify the type of behavior exhibited by each student, recording the observations on a worksheet before moving on to the next student. The investigators are in a spot where they can see the whole classroom properly. They use headphones and a prerecorded track with audible signals that indicate when to evaluate to the next student. Before data collection, the evaluators underwent a familiarization process with the measurement of this variable in the same context (i.e., teachers, students and classroom) to be assessed. This helped mitigate any potential reactivity effects that students and teachers might exhibit.

##### Cognition

2.4.2.3

The executive functions of inhibition, cognitive flexibility and working memory are evaluated as main indicators of cognitive function. These are measured using the NIH Examiner program (44) through the (i) Flanker task; (ii) Shifting task and (iii) N-Back protocols, respectively.

###### Flanker task

2.4.2.3.1

It evaluates the response inhibition and cognitive control (45). In this test, participants direct their attention to a fish located in the center of a row of five fish displayed on the screen. The fish in the center has a mark either above or below it. Each trial has a stimulus presentation time of 1,000 milliseconds. Participants are instructed to quickly indicate the direction in which the fish in the center is pointing.

###### Shifting task

2.4.2.3.2

It evaluates cognitive flexibility (44). In this test, three figures are displayed on the screen, with one figure positioned at the top and one figure in each corner. The figures are presented in different colors. During the test, the word “SHAPE” or the word “COLOR” appears on the screen, accompanied by the computer reading it aloud. The participants have to associate the figure at the top with one of the figures in the corners. In case of hearing the word “COLOR” the participant should select the figure in the corner that has the same color as the top figure. On the contrary, in case of hearing the word “SHAPE,” the participants have to select the corner figure that has the same shape of the upper figure.

###### N-back

2.4.2.3.3

It evaluates working memory (46). In this test, a first screen shows a white square located in a certain place, followed by a number that the participants are asked to read aloud. Subsequently, a second screen is shown with a white square that may be in the same or in a different location of the previous square. The participants should remember the location of the previous square.

##### Psychological health

2.4.2.4

Health-related quality of life is measured through the EuroQol five dimensions three levels (EQ-5D-3L), which has been shown to be a viable, valid and reliable tool in children and adolescents (47). The EQ-5D-3L questionnaire measures health status across five dimensions: (i) mobility; (ii) self-care; (iii) usual activities; (iv) pain/discomfort and (v) anxiety/depression. Participants are asked to rate their level of difficulty or problems in each dimension using a Likert-type scale with three response options: (i) no problem, (ii) some problems, and (iii) many problems. This questionnaire also includes a visual analog scale (VAS) to assess general health, where the participants assign a score between 0 and 100 on the VAS to indicate their current perception of their overall health.

On the other hand, self-perceived health is measured through the classic self-reported health item (48), where participants have to classify their health among the following options: “excellent” (5); “very good” (4); “good” (3); “fair” (2) and “poor” (1).

##### Motivational variables

2.4.2.5

*The Novelty Need Satisfaction Scale* (*NNSS*) was used to evaluate students novelty satisfaction (49). This scale has shown construct, discriminant and convergent validity along with measures of psychological need satisfaction and forms of motivation from self-determination. Participants are asked to rate their agreement with these five statements on a Likert-type scale ranging from 1 (strongly disagree) to 5 (strongly agree).

Enjoyment and boredom were evaluated with the *Spanish version of The Sport Satisfaction instrument (SSI)* (50). Although this scale was initially created for the sport contexts, the Spanish version was adapted to the physical education context (51), and its showed valid and reliable with adolescents. For this particular study, we replace the initial statement from physical education to math or general school context depending of the randomized group. The scale consists of eight items measuring intrinsic satisfaction, with two subscales: satisfaction/enjoyment (five items) and boredom (three items). Participants rate their agreement with the items related to fun or boredom on a five-point Likert-type scale, ranging from 1 (strongly disagree) to 5 (strongly agree).

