#### Active break intervention

2.3.1

AB intervention takes place daily and is carried out in the normal academic lessons, where two ABs per day are included in the 7th and 8th grade timetable of each secondary school. The timing of the AB is coordinated with the school management team. Whenever possible, one AB is scheduled before recess and the other after recess. It is important to note that no AB are scheduled during physical education classes or the lesson immediately following physical education. This ensures that the effect of the AB is not solely attributed to the PA performed in the preceding physical education class. The remaining class time follows the usual methodology without any variation.

The implementation of this intervention utilizes digital platform accessible to schools through individuals’ usernames and passwords. This platform has been specifically designed to facilitate the development of AB in school classes. An example of AB can be found in the following link: https://www.dropbox.com/s/dtye613hb3m3c50/VideoDescansoActivo.mp4?dl=0. This innovative tool allows to program different types of AB easily and quickly, by alternating variables such as physical exercise, its duration or intensity. Based on the findings from the review by Daly-Smith et al. (16), each AB has a duration of 5 min, of which 4 min of activity are used, including two sets of 20 s of work and 10 s of rest of four different exercises. Finally, a cool down consisting of deep breaths is performed. The activities selected for each of the AB include aerobic and strengthening activities (i.e., jumps, squats, lunges or skipping).

Teachers have access to the platform and are responsible for conducting the AB as scheduled by the research team. During the AB, students follow the instructions provided by an avatar that guides the session through the platform. To ensure the proper use of the platform, the research team provides training and support to the teachers. During the initial phase of the intervention, the research team accompanies the teachers for the first 2 weeks to ensure a smooth implementation of the AB and address any questions or concerns that may arise. This support aims to familiarize the teachers with the platform and ensure they feel confident in delivering the AB effectively.

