#### Physically active learning intervention

2.3.2

PAL intervention involves integrating PA into academic lessons, specifically within the subject of mathematics. This subject has a substantial body of evidence supporting its applicability for PAL, as it is a core subject taught in all grades of secondary education (26, 32, 33). Out of the total number of mathematics lessons taught per week in Spanish schools (four one-hour classes per week), one class per week for 16 weeks is dedicated to the PAL intervention. Each of the PAL is developed outside the classroom during the intervention.

The mathematics teacher corresponding to this intervention group, previously trained and with the constant support of the research team, oversees implementing the strategies in their academic lessons. Before each PAL class, the research team and the mathematics teacher collaborate in a meeting to determine the specific content to be covered and co-develop the activities to be included in the session. Some examples of activities used in the sessions can be found in the following free downloadable book: https://www.dykinson.com/libros/aprendizaje-fisicamente-activo-fundamentos-teoricos-y-estrategias-practicas-para-la-materia-de-matematicas-en-1o-y-2o-de-eso/9788411701617/

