### Data analysis

2.5

Data will be presented as mean and standard deviation or median and interquartile range, if applicable, for continuous variables, and frequency and percentage for categorical variables. As a cross-sectional fashion, descriptive, correlational, regression and differential analyses will be implemented. Before to implement the main analysis to test the effects of the interventions, we will test for group equivalence at baseline, by using independent samples *t*-test for continuous variables and chi square test for categorical indicators. To assess the effects of the two interventions on outcomes, repeated measured analysis will be used with the outcome measures as dependent variables in separate models, the intervention as an independent variable and controlling for potential confounders (i.e., gender). If normality analyses show non-normal distributions, the equivalent non-parametric analyses will be performed. Quantitative analyses will be completed using the SPSS 26 statistical package (IBM, Armonk, NY, USA), establishing a confidence level of 95% (*p* < 0.05).

On the other hand, the qualitative information from the semi-structured interview and the focus group will be transcribed and analyzed with the NVIVO software (55). These data will be analyzed following content analysis strategies where two phases will be differentiated. A first deductive phase aimed at detecting any type of information related to the purpose of the study. Subsequently, an inductive phase where the experiences, thoughts and reflections of teachers and students related to the AB and PAL will be identified (56).

All the analyses will be carried out considering intention to treat, keeping the participants in the group they were originally allocated and taking into consideration the CONSORT guidelines for cluster RCTs (57).

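### The enjoyment/boredom scale asks about maths or about school in general according to randomised arm, so its AB–PAL contrast, and any contrast with controls who answered the other stem, mixes intervention effect with stem

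*Protocol article*

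**What the plan says.** Section 2.4.2.5 (Motivational variables) uses an eight-item SSI: five items on enjoyment and three on boredom. The Spanish version was adapted to physical education, and for this trial the authors write: "we replace the initial statement from physical education to math or general school context depending of the randomized group".

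The arms differ in where the intervention takes place. Section 2.3.2: "PAL intervention involves integrating PA into academic lessons, specifically within the subject of mathematics". Section 2.3.1: "AB intervention takes place daily and is carried out in the normal academic lessons". Section 2.3.3: "The control group receives the usual academic lessons during the 16-weeks of intervention". No section says which SSI stem control students received.

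Section 2.5 (Data analysis) applies one approach to all outcomes: "repeated measured analysis will be used with the outcome measures as dependent variables in separate models, the intervention as an independent variable". Gender is the only confounder named. Nothing limits the SSI to arms that share a stem.

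A related sentence is in section 2.4.2.2.5: "Time-on task is evaluated in mathematics classes or the time at which the AB are to be held". It adds an observation in the following class.

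**The concern.** A between-arm comparison assumes that the same quantity is measured in each arm. Here the question itself depends on allocation. The natural reading is that PAL students rate maths and AB students rate school in general. If liking for maths and liking for school move differently between January and May, or respond differently to the same benefit, the model attributes the difference to the intervention. No covariate can repair this for AB against PAL, because stem and arm coincide. More students do not help either: they only estimate the mixed quantity more precisely.

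The Conclusion lists motivational variables among the things the trial examines, so these comparisons are likely to be reported as effects.

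**Working it through.** The article states no figure on this point, so there is none to reproduce. The check is to set the sections side by side, work out what each contrast estimates, and illustrate the size.

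**1. Which stem goes with which arm**

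| Arm | Setting (section) | SSI stem |
|---|---|---|
| PAL | maths lessons (2.3.2) | maths (inferred from setting) |
| AB | academic lessons generally (2.3.1) | general school (inferred from setting) |
| Control | usual lessons (2.3.3) | not stated |

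Dependence on arm is stated outright in 2.4.2.5. The mapping in the last column is inference from the settings.

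**2. What the AB–PAL contrast estimates**

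Let M and G be the mean scores on the maths and general-school stems without intervention. Let ΔM and ΔG be their changes from baseline, and let E be each intervention's effect as its own stem registers it.

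- Post-only difference, AB minus PAL: (E_AB − E_PAL) + (G_post − M_post). The full stem offset remains.
- Difference in change (group-by-time): (E_AB − E_PAL) + (ΔG − ΔM). If the offset is constant, ΔG = ΔM and it cancels. Differential drift does not cancel.
- E_AB and E_PAL are on different scales. PAL occupies one of four weekly maths lessons and is scored on a maths stem. AB occur twice a day and are scored on a stem covering the whole of school. Equal benefit could give unequal E, and floor or ceiling effects act in the same way.

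The same algebra applies to an intervention arm against controls who answered the other stem. Where controls answered the same stem, the extra term disappears.

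**3. Illustrative size**

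Inputs: 292 students (section 2.2). An equal split is assumed, since the text gives no arm sizes: 292/3 ≈ 97 per arm. After the article's 25% dropout: 292 × 0.75 = 219, and 219/3 = 73. Clustering is ignored. No true intervention effect is assumed. The stem differences d, in SD units, are assumptions.

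Probability of two-sided p<0.05 = Φ(d/√(2/n) − 1.96) + Φ(−d/√(2/n) − 1.96).

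For n = 97 and d = 0.2: √(2/97) = 0.1436 and 0.2/0.1436 = 1.393, so Φ(−0.567) + Φ(−3.353) = 0.286.

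| Assumed d (SD) | n = 97 per arm | n = 73 per arm |
|---|---|---|
| 0.1 | 0.11 | 0.09 |
| 0.2 | 0.29 | 0.23 |
| 0.3 | 0.55 | 0.44 |
| 0.5 | 0.94 | 0.86 |

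The nominal rate is 0.05. For a post-only contrast, d is the offset itself. For a change from baseline, d is the drift between stems. The same table then applies if the baseline–post correlation is 0.5, because the SD of change is √(2(1 − 0.5)) = 1.

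**4. Time-on-task**

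Section 2.4.2.2.5 gives two kinds of observation slot but does not tie them to arm. AB slots exclude only physical education and the lesson after it, so an AB slot may itself be a maths lesson. The SSI problem carries over only if the lesson type observed follows the arm.

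**The case against.** The other side has five arguments.

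- *Each arm is asked about the setting in which it was exposed.* This is a reasonable rationale. It supports PAL against control on maths and AB against control on general school. It does not support a model containing both AB and PAL.
- *AB against PAL is not a named hypothesis.* Correct: the objectives speak of the effects of the two interventions. But a three-level arm factor produces that contrast, and its overall test includes both arms.
- *Baseline is measured, so a stem difference cancels.* This stands for a constant offset in the group-by-time term, provided each arm keeps its stem throughout. A reader might infer that any difference between the stems would surface as an intervention effect; in that term it would not. Section 2.5 does not say which term carries the effect, so main-effect and post-only contrasts remain exposed.
- *The control arm may be sound.* A reader might infer that controls can match at most one intervention arm. The article does not support that, because it is silent on their stem and they may have completed both. A condensed article can leave this to fuller documents.
- *Time-on-task may be sound.* A reader might infer that lesson and arm coincide there too. The sentence does not mention allocation, and control classes may have been observed in both kinds of slot.

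The last two arguments narrow the point. None removes it for AB against PAL on the SSI.

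**Conclusion.** The point holds for the SSI. Stem is set by arm and the planned model has arm as its factor, so the AB–PAL contrast cannot separate the intervention effect from differential change or responsiveness of the stems. The same is true of any contrast with controls who answered a different stem. In post-only or main-effect contrasts, even a constant offset contaminates the result.

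The actual size cannot be derived from the article. Under the assumptions stated with the table, drift of 0.1 to 0.3 SD would raise the false-positive rate from 0.05 to between 0.11 and 0.55 at 97 per arm, or between 0.09 and 0.44 at 73 per arm.

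For time-on-task the problem is conditional on how observation slots were allocated. Both outcomes are secondary, and the accelerometer primary outcome is untouched. The change is worth making, but it does not threaten the trial's main result.

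**What to change.** If measurement can still be changed, give students in all three arms both stems at each wave. Compare PAL with control on the maths stem and AB with control on the general-school stem. The cost is eight extra items per wave.

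Measurement was scheduled for January to June 2023, so the analytic route is more likely to be the one available:

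- State which stem or stems control students answered.
- Restrict between-arm SSI comparisons to arms that answered the same stem, and base them on change from baseline.
- Report any unmatched arm as within-arm change only.
- Drop the AB–PAL contrast on the SSI.

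For time-on-task, state which lesson types were observed in each arm. If lesson type followed the arm, compare each intervention arm only with control observations from the same lesson type.

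The analytic route costs a short addition to the analysis plan and the loss of the AB–PAL contrast on a secondary outcome. If controls answered only one stem, the comparison of the unmatched arm with control is lost as well.
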